### Methods and equipment used for screening

All invasive PoC tests are conducted by pharmacists who have received structured training and technical guidance from the study team. Blood pressure is recorded using a validated automatic device and participants will take three consecutive seated measurements after a five-minute rest period.

For screening the following equipment will be used:

Home-based albuminuria testing: Siegmund Care GmbH, Oberottmarshausen, Germany.Pharmacy based albuminuria testing (UACR): Afinion 2, Abbott Rapid Diagnostics Germany GmbH, Köln, Germany.HbA1c: A1CNow+, Medic-SH, Reinfeld, Germany.LDL-C: PTS CardioCheck Plus, Medic-SH, Reinfeld, Germany.Blood pressure: M2 Comfort, OMRON, Kyōto, Japan.

### Data transmission and analysis

The collected screening parameters are securely transmitted to the study center. The digital study platform, including the eCRF and data infrastructure, is provided by meditrova GmbH (Rostock, Germany). It is accessible via smartphone, tablet or personal computer through the internet and an application (*App*). After screening completion, a physician at the study center will review and analyze the data. Based on the results, patients are further stratified:

For unremarkable screening results a digital follow-up is conducted.For positive screening results a confirmatory testing and digital follow-up is conducted.

### Confirmatory testing

Participants are invited to undergo confirmatory assessment if screening results meet at least one of the predefined thresholds: systolic blood pressure ≥ 140 mmHg and/or diastolic blood pressure ≥ 90 mmHg, positive urine albuminuria test (corresponding to an albuminuria ≥A2 and urine-albumin-creatinine-ratio of ≥ 30 mg/g), a non-HDL-C ≥ 5.7 mmol/l or HbA1c ≥ 5.7% for patients without and ≥ 8.5% for patients with known diabetes (Supplementary Figures S1-4 [23–26]). In case of critical values at screening, pharmacists will be guided by an emergency algorithm (Supplementary Figure S5).

Confirmatory testing will be performed at the study center to enable standardized reassessment. To ensure representative coverage of both urban and rural regions, participating pharmacies will be selected accordingly, allowing the study to capture regional heterogeneity in patient presentation and healthcare access. In this context, ten pharmacies located at greater geographical distance (> 30 km) from the study center will be included.

At the study center visit, all previously screened parameters will be reassessed using standardized laboratory methods. In addition, 24-hour ambulatory blood pressure monitoring (ABPM) or 7-day home-based blood pressure monitoring (HBPM) will be conducted. Blood measurement of creatinine, CRP and lipoprotein(a) will be taken for improved precision of the risk assessment. The patient pathway is visualized in Fig. 1.

**Fig. 1 Fig1:**
[figure not shown]
Flow chart of study recruitment, testing and follow-up. GP, General Practitioner; PoC-Test, Point-of-Care-Test; HDL, high-density lipoprotein; DM, Diabetes mellitus; Obesity defined as (BMI ≥30kg/m² or waist circumference ≥ 88cm for women or ≥ 102cm for men); * if confirmatory testing is not feasible at the GP, participants can conduct confirmatory testing at the study center

### Patient risk report and digital follow-up

Based on medical history, screening results, and, if available, confirmatory testing outcomes, an individualized risk report based on current national and international guidelines is generated and made accessible for the participant through the digital study platform. The report will provide a structured summary of all relevant findings, with a particular focus on estimated cardiovascular risk (SCORE2, SCORE2-OP, SCORE2-Diabetes, SMART2-Score, depending on applicability) and risk of kidney replacement therapy (kidney failure risk equation), and will serve as a structured basis for follow-up consultations within the primary care system [27–30]. Participants with unremarkable screening results will receive a report providing general evidence-based recommendations for general CKM syndrome risk reduction.

### Data storage

Data will be pseudonymized and stored on servers of the study center for 10 years after study completion. Study investigators will have access to information for re-identification. Participants may withdraw consent at any time and request deletion of their data. All data shared for research will be anonymized.

### Sample size and statistical analysis

The planned sample size of 1000 participants allows for reliable estimation of key outcomes with 95% confidence intervals with an estimation error of approximately ± 5%. With an expected prevalence of 50% of risk factors and 10 pharmacies in the region of the study center, we expect 250 participants with indication for confirmatory testing at the study center. At an expected attrition of 20%, 200 participants should complete confirmatory testing. This allows for determination of false-positive rates and test specificity with acceptable precision (± 10%). Attrition in the GP-confirmatory testing arm is expected to be higher, but will be minimized through repeated digital or telephone prompts and, if necessary, invitation for testing at the study center. Statistical analysis will be descriptive, using frequency tables, means (± standard deviation), medians (± interquartile range) for Likert-Scale analysis, and proportions with 95% confidence intervals. Diagnostic metrics (sensitivity, specificity, PPV, NPV) will be determined. Sensitivity of the PoC test can be assessed based on the results from the confirmatory testing. Scale scores for implementation metrics will be calculated as the mean of the respective items, with higher values indicating greater agreement and lower values indicating greater disagreement.

Feasibility and clinical outcomes will be summarized overall and, where appropriate, descriptively at pharmacy level. Pharmacy-level summaries will include recruitment numbers, screening completion rates, confirmatory testing uptake, diagnostic yield, and implementation scores. Baseline pharmacy characteristics will be used to contextualize variation across pharmacies, whereas pharmacy-level implementation process metrics will be interpreted as outcomes of the implementation process. Given the limited number of participating pharmacies, these analyses will be exploratory and hypothesis-generating. Confirmatory inference regarding pharmacy-level predictors is not planned.

Implementation outcomes will be analyzed separately for each implementation instrument and domain. AIM, FIM, and NoMad assess conceptually distinct implementation constructs, including acceptability, feasibility, and normalization/sustainability. Therefore, no combined implementation score or omnibus test will be used. For each domain, median Likert-scale scores and interquartile ranges will be reported. In addition, one-sided one-sample Wilcoxon signed-rank tests will be used to assess whether domain scores exceed the neutral midpoint of the scale, using the null hypothesis that the median domain score is ≤ 3. Given the exploratory nature of this pilot implementation study and the domain-specific interpretation of implementation outcomes, no formal multiplicity adjustment is planned. Results will be interpreted separately by domain and in the context of the overall implementation pattern.

The unadjusted NNS will be calculated as the number of participants with completed screening divided by the number of participants with at least one previously unknown or insufficiently managed CKM risk factor identified during screening. For primary outcome, a pre-specified PPV-adjusted NNS will be calculated using the positive predictive value estimated among screen-positive participants undergoing confirmatory testing at the study center. Participants without available confirmatory testing will not be included in the estimation of the PPV. Stratified NNS according to pharmacy-prompted or self-referral recruitment will be further reported.

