### Study setting and pharmacy selection

The study takes place in the outpatient setting with a planned number of 20 participating pharmacies. This number was chosen pragmatically for the pilot implementation phase to balance sufficient recruitment capacity with feasibility of onboarding, monitoring, technical support, and confirmatory follow-up. Each pharmacy is expected to recruit approximately 50 participants, resulting in a total planned sample size of 1,000 participants.

Pharmacies will be selected in collaboration with the Pharmacists’ Association of Schleswig-Holstein. The Association invited community pharmacies in Schleswig-Holstein to express interest in participation. From this pool of interested pharmacies, sites will be selected purposively according to predefined implementation-relevant criteria. First, we aim to include 10 pharmacies located in the region of the study center and 10 pharmacies located at greater distance from the study center. Second, within each of these two groups, we aim to include five pharmacies with customer restroom facilities allowing on-site urine albumin-creatinine ratio (UACR) testing and five pharmacies without such facilities, resulting in 10 pharmacies with and 10 pharmacies without on-site UACR testing capacity. Third, pharmacies will be selected to ensure broad geographic coverage across Schleswig-Holstein, including northern, southern, western, and eastern regions of the federal state.

This selection strategy is not based on random sampling and is not intended to generate a representative sample of all German community pharmacies. Rather, it is a purposive implementation-oriented sampling strategy designed to capture relevant heterogeneity in pharmacy infrastructure, distance to the study center, and regional accessibility within Schleswig-Holstein.

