### Primary outcomes

The study will assess three primary outcomes:

(I)Participant-level feasibility is assessed by screening completion rates of participants who provided informed consent. The outcome is defined as completion of the structured questionnaire, performance of blood pressure measurement and PoC-testing for dyslipidemia and HbA1c. The study aims for an overall completion rate ≥ 70% based on the reported use of primary care screenings and prospective feasibility on the national level in Germany.(II)Implementation outcomes from the pharmacy perspective are evaluated for the implementation domains acceptability, feasibility, and sustainability. The outcome is evaluated using validated instruments, including the Acceptability of Intervention Measure (AIM), the Feasibility of Intervention Measure (FIM), and the Normalization Measure Development Questionnaire (NoMad) to assess sustainability (Supplementary Tables 1 and NoMad Questionnaire) [16–19]. These instruments use standardized self-administered questionnaires completed by pharmacy staff that are rated on Likert scales. Validated German versions will be used. For each domain, the outcome criterion is defined by a null hypothesis assuming a median Likert-scale score ≤ 3. Rejection of the null hypothesis will be interpreted as evidence of sufficient implementation performance under routine practice conditions.(III)The medical screening yield is quantified by the number needed to screen (NNS) to identify at least one previously unknown or insufficiently managed CKM syndrome risk factor. These are defined as non-HDL cholesterol ≥ 5.7 mmol/L for known dyslipidemia or lipid-lowering therapy, HbA1c ≥ 8.5% in participants with known diabetes mellitus, positive albuminuria test without RASi or SGLT2i therapy in participants with CKD, or blood pressure ≥ 140/80 mmHg for participants with known hypertension. A NNS ≤ 5 will be considered as indicative of a clinically meaningful detection efficiency of the multi-parametric screening approach. Further, a NNS between 5 and 10 will be considered an exploratory finding indicating the need for potential refinement or modification of the screening strategy. An observed NNS > 10 will be interpreted as an unfavorable feasibility outcome under routine practice conditions.

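### The ±5% precision statement and the staff-level Wilcoxon tests make no allowance for clustering in 20 pharmacies; at a 50% proportion, ±5% holds only up to an intraclass correlation of about 0.03

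*Protocol article*

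**What the plan says.** On the design, the Protocol article (Study setting and pharmacy selection) gives a "planned number of 20 participating pharmacies", and "Each pharmacy is expected to recruit approximately 50 participants, resulting in a total planned sample size of 1,000 participants". The sites are chosen purposively so that they differ in infrastructure, distance from the study center and region.

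On precision, Sample size and statistical analysis states: "The planned sample size of 1000 participants allows for reliable estimation of key outcomes with 95% confidence intervals with an estimation error" of about ±5%. No ICC or design effect is given. Proportions are to carry 95% confidence intervals, with no interval method named. Pharmacy enters the analysis only through descriptive, exploratory summaries.

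On the implementation outcomes, Primary outcomes (II) relies on "standardized self-administered questionnaires completed by pharmacy staff". The analysis is that "one-sided one-sample Wilcoxon signed-rank tests will be used to assess whether domain scores exceed the neutral midpoint of the scale", and rejection is the criterion for sufficient implementation performance. The number of respondents per pharmacy, the unit of analysis and the significance level are not given.

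**The concern.** The document itself gives reasons to expect outcomes to be correlated within pharmacies:

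- Equipped pharmacies do all tests at the first visit. Elsewhere HbA1c and lipids wait for a second appointment (Data source and collection at screening). Both tests are part of the definition of completion, so completion depends partly on the pharmacy.
- Pharmacies have latitude in whom they invite (Participant selection), so yield depends partly on the pharmacy.
- Colleagues who rate the same local implementation share what they are rating.

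If this correlation is positive and ignored, intervals for the completion rate, the yield and the positive predictive value (PPV) understate the uncertainty, and a signed-rank test over individual staff counts one pharmacy's experience several times. The Discussion and Limitations intend the results to inform scaling and a larger study, which is inference beyond these 20 sites.

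**Working it through.** **Inputs from the document:** n = 1,000, 20 pharmacies, m = 50 per pharmacy, expected prevalence 50%, completion target 70%, NNS 5 (a yield of 20%), and about 200 confirmatory results expected through 10 pharmacies near the study center. **Assumed, because not stated:** ICC 0.01–0.10 for participants and 0.05–0.30 for staff, 1–5 staff respondents per pharmacy, one-sided test level 5%.

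**1. The plan's own figure.** Under independence the half-width is 1.96 × √(p(1−p)/n):

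- p = 50%: 1.96 × √(0.25/1000) = ±3.10 points
- p = 70%: 1.96 × √(0.21/1000) = ±2.84
- p = 20%: 1.96 × √(0.16/1000) = ±2.48

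So ±5 is not reproduced from n = 1,000; at p = 50% it would need only 385 independent people. The difference is in the conservative direction.

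**2. The clustering that ±5 can absorb.** Design effect = 1 + (m−1) × ICC = 1 + 49 × ICC. Setting the half-width to 5:

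| p | implied design effect | largest ICC (normal) | largest ICC (t, 19 df) |
|---|---|---|---|
| 50% | (5/3.10)² = 2.60 | 1.60/49 = 0.033 | 0.026 |
| 70% | (5/2.84)² = 3.10 | 2.10/49 = 0.043 | 0.035 |
| 20% | (5/2.48)² ≈ 4.07 | 3.07/49 = 0.063 | 0.052 |

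An ICC of 0.033 at p = 50% means that true pharmacy rates vary with a standard deviation of √(0.033 × 0.25) ≈ 9 points. At 70% and 20% the limits correspond to about 9.5 and 10 points.

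**3. Half-width and coverage over a range of ICC.** The half-widths are for p = 50%. The coverage of an ordinary 95% interval is 2Φ(1.96/√design effect) − 1 and does not depend on p.

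| ICC | design effect | half-width, normal | half-width, t (19 df) | coverage of ordinary interval |
|---|---|---|---|---|
| 0.01 | 1.49 | ±3.8 | ±4.0 | 89% |
| 0.02 | 1.98 | ±4.4 | ±4.7 | 84% |
| 0.03 | 2.47 | ±4.9 | ±5.2 | 79% |
| 0.05 | 3.45 | ±5.8 | ±6.2 | 71% |
| 0.10 | 5.90 | ±7.5 | ±8.0 | 58% |

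At ICC 0.05 the normal half-width is ±5.3 at p = 70% and ±4.6 at p = 20%.

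**4. The confirmatory sample behind the PPV.** The plan's counts reproduce: 1,000 × 0.5 × 0.5 = 250, and 250 × 0.8 = 200. Independence gives ±6.9 points at p = 50%. With 20 per pharmacy from 10 pharmacies and ICC 0.05, the design effect is 1 + 19 × 0.05 = 1.95. The half-width becomes 6.93 × √1.95 = ±9.7, or ±11.2 with t on 9 df.

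**5. The Wilcoxon test.** Simulation: 20 pharmacies, true median 3, scores rounded to 0.25, one-sided 5%, 3,000 trials per cell. Rejection rates:

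| staff per pharmacy | ICC 0.05 | 0.10 | 0.20 | 0.30 |
|---|---|---|---|---|
| 1 | 5.1% | 5.4% | 5.0% | 5.1% |
| 2 | 5.2% | 5.4% | 6.6% | 7.5% |
| 3 | 6.1% | 6.5% | 8.4% | 10.4% |
| 5 | 6.0% | 8.1% | 10.9% | 13.8% |

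**The case against.** Several points on the other side stand.

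- The article names no interval method, and a variance estimator is commonly left to an analysis plan that is not shown. That the intervals will be computed as if independent is inferred from silence, so they cannot be called too narrow outright. The named one-sample Wilcoxon test is firmer ground, because in its standard form it assumes independent observations.
- A reader might infer that ±5% is wrong. The document does not support that: ±5 is wider than independence gives and leaves room for a design effect of 2.6, and for more at the proportions where the cut-offs sit.
- A reader might infer that clustering could overturn the completion or NNS verdicts. Primary outcomes reads both on observed values, and no rule uses a confidence limit.
- A reader might infer that the Wilcoxon tests reject too often as planned. That needs more than one respondent per pharmacy and correlated ratings. The plural wording makes this likely but does not fix it. At two respondents and low ICC the excess is negligible.
- The sites were chosen purposively. If inference is confined to these 20 as fixed strata, the coverage argument weakens. Part of the between-pharmacy variance may also be explained by the selection cells (distance, restroom), which the design effects above ignore.

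Two things remain. The document fixes a precision claim and a test, and neither mentions the nesting. And its stated use of the results reaches beyond these sites. Calling the study an exploratory pilot does not restore coverage.

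**Conclusion.** The concern holds in conditional form. The stated ±5% rests on an unstated allowance for clustering that is used up at an ICC of about 0.033 when p = 50%, 0.043 at 70% and 0.063 at 20%, and somewhat sooner with t-based limits. It is at risk, not refuted.

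If ordinary intervals are used and generalised beyond the 20 sites, coverage is about 84% at ICC 0.02 and 71% at 0.05. What suffers is the certainty attached to the completion rate and the NNS, not their reading against the cut-offs. For the implementation outcome the test itself is the criterion, so its error rate matters directly: about 5–14% with two to five raters per pharmacy and ICC 0.05–0.30, and about 5% with one.

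All ICCs, the rater numbers and the 5% level are assumptions. The plan should be changed, but nothing here invalidates the study.

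**What to change.** - **Precision statement.** Give the assumed ICC with it: ±3.1 points if independent, about ±4 to ±8 for ICC 0.02–0.10 at p = 50%.
- **Intervals for completion rate, yield and PPV.** Use pharmacy as the cluster, with t-based degrees of freedom.
- **Primary PPV-adjusted NNS.** Inverting the limits of the yield proportion serves only the unadjusted NNS. Use a cluster bootstrap that resamples pharmacies and recomputes yield and PPV together. State that the PPV is expected mainly from the 10 pharmacies near the study center, so it rests on fewer clusters.
- **Implementation scores.** State how many staff respond per pharmacy and what the unit of analysis is. Run the Wilcoxon test on one mean score per pharmacy, or use a clustered signed-rank test.

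The cost is analysis wording and a few lines of code. Intervals become wider and p-values larger; no extra participants are needed.

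### Because screen-negatives get no reference test, sensitivity, specificity and NPV of the multiparametric screen are not identified, and per-test sensitivity and specificity are verification-biased

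*Protocol article*

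**What the plan says.** Who is verified (Protocol article, Confirmatory testing): "Participants are invited to undergo confirmatory assessment if screening results meet at least one of the predefined thresholds". The section Data transmission and analysis splits participants the same way: "For positive screening results a confirmatory testing and digital follow-up is conducted", whereas "For unremarkable screening results a digital follow-up is conducted". The follow-up column of Table 2 lists medication, GP visits, resulting changes and satisfaction, and no reference measurement.

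What is measured at the study-center visit (Confirmatory testing): "all previously screened parameters will be reassessed using standardized laboratory methods". So an invited participant also gets a reference result for the tests on which they were negative.

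What is promised (Sample size and statistical analysis): "we expect 250 participants with indication for confirmatory testing at the study center", of whom 200 are to complete. Then: "This allows for determination of false-positive rates and test specificity with acceptable precision", put at ± 10%. Then: "Diagnostic metrics (sensitivity, specificity, PPV, NPV) will be determined" and "Sensitivity of the PoC test can be assessed based on the results from the confirmatory testing". The section Exploratory outcomes applies these metrics both to the multiparametric screen and to each test category.

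The Missing data section leaves anyone without a confirmatory result for a parameter out of that parameter's PPV and accuracy calculations.

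**The concern.** Specificity needs true negatives, sensitivity needs false negatives, and NPV needs both. All of these are people with a negative test and a reference result. The pathway gives no reference test to anyone negative on every test, yet the sample-size section presents specificity as estimable with stated precision and sensitivity as following from confirmatory testing.

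If the text is followed, the trial would report accuracy figures for the screen that are fixed by the design, and per-test figures shifted in a predictable direction. The article wants its results to inform larger programmes and policy, so such figures could be taken at face value. The Limitations section covers selection, healthy-volunteer and pharmacy-level bias, but not partial verification.

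**Working it through.** **1. The plan's own figures.** Inputs from Sample size and statistical analysis: 1000 participants, 10 of 20 pharmacies near the center, 50% with an indication, 20% attrition.
- 1000 × 10/20 × 0.50 = 250; 250 × 0.80 = 200. Both reproduce.
- 95% half-width = 1.96 × √(p(1−p)/n). At p = 0.5: n = 200 gives ±6.9 points and n = 100 gives ±9.8; ±10 needs n = 97.

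The arithmetic is sound. The question is which quantity it describes.

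**2. The whole screen.** All 200 verified participants are screen-positive, so TN = FN = 0.
- Sensitivity = TP/(TP + 0) = 100%.
- Specificity = 0/(0 + FP) = 0%, so 1 − specificity = 100%.
- NPV = 0/0, undefined.
- PPV = TP/200, which is informative.

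To show what stays unknown, take 50% screen-positive (the plan's figure) and assume PPV = 0.70. The data say nothing about NPV, so let it vary:
- NPV 0.70: sensitivity 0.35/(0.35 + 0.15) = 0.70; specificity 0.35/(0.35 + 0.15) = 0.70.
- NPV 0.95: sensitivity 0.35/(0.35 + 0.025) = 0.93; specificity 0.475/(0.475 + 0.15) = 0.76.

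The observed data would look the same in both cases.

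**3. A single test.** Let q be the share of that test's negatives who are positive on another test and so are verified. Assume q does not depend on true status. All test-positives are eligible for verification.
- Apparent specificity = spec·q/(spec·q + 1 − spec).
- Apparent sensitivity = sens/(sens + (1 − sens)·q).

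| q (assumed) | True specificity 90% appears as | True sensitivity 70% appears as |
|---|---|---|
| 30% | 0.27/0.37 = 73% | 0.70/0.79 = 89% |
| 40% | 0.36/0.46 = 78% | 0.70/0.82 = 85% |
| 50% | 0.45/0.55 = 82% | 0.70/0.85 = 82% |

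The article gives no per-test positive rates, so q is an assumption. If the 50% is read as the any-positive share and π is the test's own positive rate, then q = (0.5 − π)/(1 − π). For example, π = 10% gives q = 44% and π = 25% gives q = 33%. Values below 30% arise once π exceeds about 29%, and the bias is then larger.

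**4. Simulation check.** Four tests, 1,000,000 participants; assumed prevalences 25, 12, 10 and 15%, sensitivity 0.80, specificity 0.93; only participants with any positive test verified.
- Sensitivity appears as 0.86 to 0.91 and specificity as 0.82 to 0.87.
- NPV is unbiased with independent conditions, and about 1 to 3 points low with a latent correlation of 0.3.
- PPV is unbiased in both settings.
- Of 200 verified participants, 103 to 148 are negative on a given test, so the per-test tables can be filled.

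**5. Precision of PPV.** The ±6.9 points belongs to the PPV of being positive on any test. A parameter-specific PPV rests only on positives for that test. In the simulation these number 52 to 97 of 200, which gives ±13.6 to ±10.0 points at p = 0.5. None of these half-widths allows for clustering by pharmacy.

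**The case against.** The strongest reply is that the disputed sentences speak of test specificity and of the sensitivity of the PoC test. Since every screened parameter is reassessed at the study center, verified test-negatives do exist for each test. This stands. A reader might infer that only PPV can be estimated at any level; the documents do not support that. Per-test values are computable. They describe people positive on at least one test, and do not carry over to all screened participants.

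Second, the false-positive rates might mean the unconfirmed share of positives, 1-PPV. That would be estimable to about ±7 points, within the stated ± 10%. The pairing with specificity makes the other reading more natural, and neither reading rescues specificity or sensitivity.

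Third, these metrics are not primary: Exploratory outcomes lists them as exploratory and the abstract as secondary. A reader might infer that the primary yield result is compromised. It is not, because the PPV-adjusted NNS needs only PPV.

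Fourth, a reader might argue that the 200 is overstated because the completion target is only 70%. That target is a minimum aim, not a forecast. Even at that floor, 350 × 0.5 × 0.8 = 140 verified participants give ±8.3 points, still inside ± 10%.

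A separate analysis plan could not fully repair the matter. Participants negative on every test have zero chance of verification, so no reweighting of the verified group recovers them without an untestable assumption. Excluding unverified participants, as the Missing data section does, leaves the bias in place.

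**Conclusion.** The point holds in two parts. For the multiparametric screen, sensitivity, specificity and NPV are not identified; this follows from the pathway alone and needs no assumption. For single tests, sensitivity is biased up and specificity down. The illustration of 90% appearing as 78%, and 70% as 85%, rests on an assumed q of 40% unrelated to true status; the simulation gives the same direction under its own assumed inputs. Per-test NPV is little affected there.

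The ± 10% statement is correct arithmetic attached to the wrong quantity. It fits the any-positive PPV. This should be fixed, because the article claims a property that the design does not have. No primary outcome depends on it.

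**What to change.** In Sample size and statistical analysis, replace three sentences: the one on false-positive rates and specificity, the one listing the four diagnostic metrics, and the one on sensitivity. Suggested text: 'Confirmatory testing of screen-positive participants supports estimation of PPV and 1-PPV. With 200 verified participants, the 95% confidence interval for the PPV of any positive result is about ±7 percentage points at a PPV of 50%, before allowance for clustering. Parameter-specific PPVs rest on fewer positives and are less precise. Sensitivity, specificity and NPV of the multiparametric screen are not estimable, because screen-negative participants receive no reference test.'

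In Exploratory outcomes, remove sensitivity, specificity and NPV for the multiparametric screen. If per-test values are kept, label them as conditional on at least one positive test, verification-biased, and not generalisable to all screened participants.

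The cost is wording and a change in reporting; no procedure or sample size changes. If the sponsor wants whole-screen accuracy, a random sample of screen-negatives would need reference testing, which is a design change and not part of this fix.

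### The signed-rank test matches the stated null (median domain score ≤ 3) only under symmetry, so a domain can be declared sufficient with an observed median of 3 or below

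*Protocol article*

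**What the plan says.** Under *Primary outcomes*, outcome II covers acceptability, feasibility and sustainability as seen by pharmacy staff. The criterion is about a median: "For each domain, the outcome criterion is defined by a null hypothesis assuming a median Likert-scale score ≤ 3". The decision rule follows at once: "Rejection of the null hypothesis will be interpreted as evidence of sufficient implementation performance under routine practice conditions".

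*Sample size and statistical analysis* attaches the test: "one-sided one-sample Wilcoxon signed-rank tests will be used to assess whether domain scores exceed the neutral midpoint of the scale". That section repeats the same null, again placed on the median of the domain score with 3 as its upper bound. The variable tested is an average of items: "Scale scores for implementation metrics will be calculated as the mean of the respective items". Descriptive results stand beside the test: "For each domain, median Likert-scale scores and interquartile ranges will be reported".

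The article states no symmetry assumption. It does not require the observed median to exceed 3 before sufficiency is claimed.

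**The concern.** The signed-rank test weighs each deviation from 3 by its rank. If scores are symmetric about their median, testing that weighted balance is the same as testing the median. Without symmetry, the test responds to the pseudo-median (the median of all pairwise averages, or Hodges-Lehmann location), which can lie above 3 while the median does not.

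Averages of a few Likert items are bounded and fall on a coarse grid. A uniformly neutral respondent scores exactly 3. Skew and clustering at 3 are therefore realistic, above all in a borderline domain, where the criterion has to decide something.

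At stake is one of three primary outcomes. The results table could show a median at or below the null value and a claim of sufficient implementation for the same domain. The article gives the decision to the test and does not say what happens when the two disagree. Its *Limitations* section makes demonstrated feasibility part of the case for a larger study.

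**Working it through.** **Inputs.** From the article: the test, its one-sided direction, the null (median ≤ 3), the rule (rejection means sufficient) and the score (item mean). Assumed: a one-sided level of 0.05, and 20 to 60 respondents. The article gives no respondent count, only "standardized self-administered questionnaires completed by pharmacy staff that are rated on Likert scales" and a "planned number of 20 participating pharmacies". It gives no figure for this test that could be reproduced.

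**Example 1: n = 20, eleven 3s and nine 4s.** The 10th and 11th ordered scores are both 3, so the median is 3.0.
- Differences from 3: eleven zeros and nine equal positive values. Exact one-sided p = 2⁻⁹ = 0.00195. Normal approximation: z = (9r − 4.5r)/(1.5r) = 3, p = 0.00135.
- Pseudo-median: of the 20 × 21/2 = 210 pairwise averages, 66 equal 3, 99 equal 3.5 and 45 equal 4. The middle one is 3.5.
- Exact binomial test of scores above 3, with 3s counted as not exceeding: P(X ≥ 9 | 20, 0.5) = 0.748.

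**Example 2: n = 21, eleven 2.75s and ten 4s.** The 11th ordered score is 2.75, so the median is 2.75, below the null boundary.
- Mid-ranks of the absolute differences: 6 for the eleven small ones, 16.5 for the ten large ones. W⁺ = 10 × 16.5 = 165. Null mean = 231/2 = 115.5. Null variance = (11 × 6² + 10 × 16.5²)/4 = 779.6, SD 27.9.
- z = (165 − 115.5)/27.9 = 1.77, p = 0.038. Exact permutation p = 0.036.
- Pseudo-median: of 231 pairwise averages, 66 equal 2.75, 110 equal 3.375 and 55 equal 4. The middle one is 3.375.

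Example 1 rejects at 0.05 and at 0.025; example 2 rejects only at 0.05.

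**Are the 3s the cause?** No. Example 2 contains none. In example 1 the Pratt treatment, which ranks the zeros before removing them, gives the same p. It can shift a borderline result: nine 2.75s, two 3s and nine 4s (median 3.0) give an approximate p of 0.035 with zeros dropped and 0.061 with Pratt.

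**Rejection rates, one-sided 5%, true median 3**

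| Scores | n = 20 | n = 40 | n = 60 |
|---|---|---|---|
| Right skew: half on 2.5, 2.75; half on 3.25, 3.5, 3.75, 4 | about 23% | about 39% | about 51% |
| Mirror image (left skew) | 1% or less | 1% or less | 1% or less |
| Shifted exponential, no ties | 16% | 25% | 36% |
| 2/3/4/5 with 0.10/0.45/0.35/0.10 | 70% | 97% | nearly 100% |
| Symmetric 2/3/4 with 0.25/0.50/0.25 | 2.6% | 3.3% | 3.3% |

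Repeat runs of the first row gave 23–24%, 37–40% and 51–53%. In that row any value from 2.75 to 3.25 is a median, so 3 is a convention; in rows three and four the median is uniquely 3. Row four uses whole numbers, a coarser grid than item means.

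**What an observed-median condition removes.** In one run of the first row (24%, 37%, 53%), the test rejected with an observed median of 3 or less in 0.1%, 3% and 11% of trials. With the condition added, about 24%, 34% and 42% would still reject. The condition ends the visible contradiction but does not turn the procedure into a level-5% test of the median. The hypothesis therefore has to be restated as well.

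**Power of the binomial alternative.** Assume scores symmetric about 3.25, with 20% at exactly 3 and 15% below, so 65% exceed 3. At n = 20 rejection needs 15 or more: P(X ≥ 15 | 20, 0.65) = 0.25. The signed-rank test had 90% to 96% power, depending on the spread assumed. At n = 40 the binomial test needs 26 or more and has power 0.57, against over 99%.

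**The case against.** The strongest defence is that the inflation depends on a chosen direction of skew. That is right: left skew makes the test conservative, symmetry keeps its level, and nothing in the article says that staff scores will be right-skewed around neutral. With medians well above 3 the conclusion would not change.

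A reader might infer that the test discards neutral answers and that this drives the problem. The article states no handling of scores equal to 3, which is a detail that an analysis plan can settle, and the check shows that it is neither the cause nor the cure.

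A reader might also infer that the test must be replaced by a sign test. The power figures argue against that. A conventional sign test that drops the 3s does not help either: on example 1 it also gives p = 0.002.

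It can also be said that the article calls the pilot exploratory, reports medians and interquartile ranges alongside, and reads results against the overall pattern. Nine scores above neutral, eleven neutral and none below is indeed some evidence of a shift. These points soften the consequence. They do not cancel a rule that defines a primary outcome on the median and converts rejection directly into sufficiency.

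**Conclusion.** The concern holds in limited form. The null, the test and the decision rule are all fixed in the article, and they agree only if scores are symmetric about their median. Otherwise sufficiency can be declared with an observed median of 3.0 (p about 0.002) or 2.75 (p about 0.04). With right skew and a true median of 3, the rejection rate was about 23% to 51% instead of 5%.

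Those rates rest on assumed score distributions, 20 to 60 respondents and a one-sided 5% level. The two worked examples need only the level. The documents do not support the broader statements that the test never addresses the median, or that it inflates error for skewed scores in general. The point deserves correction because it concerns a primary outcome and is cheap to repair.

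**What to change.** Keep the one-sided signed-rank test, and make three changes in *Primary outcomes* and *Sample size and statistical analysis*:

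1. State the tested null as a pseudo-median (Hodges-Lehmann location) of at most 3.
2. Claim sufficiency for a domain only if the test rejects and the observed median exceeds 3.
3. Describe rejection itself as scores lying above neutral.

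As a sensitivity analysis of the median null, report an exact binomial test of scores above 3 against all non-missing scores, with 3s counted as not exceeding. State that its power is much lower at about 20 respondents.

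The cost is wording in two sections, best settled before questionnaire data are analysed. The downside is a slightly stricter success rule.
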